**ABSTRACT**

**Rationale:** Change of practice environment and an interdisciplinary team is needed to implement evidence-based diabetes care which requires risk stratification, periodic assessments, education and treatment to targets.

**Hypothesis:** The use of a web-based disease management program (Joint Asia Diabetes Evaluation (JADE) Program) delivered by a doctor-nurse-HCA team reduces the incidence of all diabetes-associated clinical endpoint and improves control of risk factors compared to usual care (DIAbetes MONItoring Database (DIAMOND) group) in type 2 diabetes.

**Objective:** To compare structured care using the JADE portal versus usual care using the DIAMOND portal on incidence of all-diabetes related events, physical and psychological health.

**Study design:** A multicentre, randomized, integrated disease management program

**Setting and patients:** 600 patients from each site will be randomized to the JADE group (n=300) or the DIAMOND group (n=300) and followed up for at least 24 months.

**Intervention:** All patients will undergo comprehensive assessment (CA) guided by the templates in the respective portal at baseline, month 12 and 24. The JADE group will be further managed by a doctor-nurse-HCA team guided by the JADE portal with risk stratification program and recommendation to different care protocols with predefined follow up (FU) schedules, information sharing and decision supports.

**Outcome measures:** Primary composite outcomes include all diabetes-related clinical events; secondary composite outcomes include control of risk factors and tertiary composite outcomes include behavioral changes, psychological health, quality of life and cost-effective analysis.

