## **SETTING AND PATIENTS**

In this program, 600 consecutive type 2 diabetic patients will be recruited from each participating centre during a 6-8 month period, with randomization to either the JADE or DIAMOND group in a 1:1 ratio.

*Inclusion criteria*

- 1) Type 2 diabetic patients who are willing or can be persuaded to return for 'regular' follow-up at 3-4 monthly intervals
- 2) Aged  $\geq 18$  years
- 3) Patients with newly diagnosed or established disease, treated with lifestyle modification or blood glucose lowering drugs including oral agents with or without insulin
- 4) For newly diagnosed type 2 diabetic patients, their plasma glucose levels should be:
  - a) Fasting plasma glucose (PG)  $\geq 7.0$  mmol/L on 2 or more occasions, and/or
  - b) Random or 2-hour PG  $\geq 11.1$  mmol/L (after 75 gram oral glucose tolerance test) on 2 or more occasions, and/or
  - c) HbA1c  $\geq 6.5\%$

*Exclusion criteria*

- 1) Type 1 diabetes defined as a history of ketosis at diagnosis [acute symptoms with heavy ketonuria ( $>3+$ ) or ketoacidosis] or continuous requirement of insulin within one year of diagnosis (38).
- 2) Patients with reduced life expectancy (e.g. less than 6 months) due to recent diagnosis of advanced cancers (e.g. within last 2 years) and other life-threatening conditions.
- 3) Patients with a mental condition rendering them unable to understand the nature, scope, and possible consequences of the study.
- 4) Patients actively enrolled in another intervention study.
- 5) Patients who are unwilling to return for regular follow up.

**OUTCOME MEASURES***Composite primary endpoint (CRF (1-5))*

- 1) Incidence of all diabetes-related endpoints including:
  - a) cardiovascular events (acute myocardial infarction, revascularisation procedures, heart failure, unstable angina, arrhythmia, stroke, transient ischemic attacks requiring hospital admissions) and related death
  - b) chronic kidney disease (eGFR  $< 60$  ml/min/1.73m^2) or end stage renal disease (dialysis and/or eGFR  $< 15$  ml/min/1.73m^2) and related death
  - c) visual impairment (corrected visual acuity of 20/200 or worse) or eye surgery (cataract removal, retinal surgery and vitrectomy)

- d) lower extremity amputation or foot ulcers requiring hospitalizations
- e) major infections – pulmonary and non-pulmonary requiring hospitalizations
- f) all-site cancers
- g) death

Composite secondary endpoint

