## SAMPLE SIZE CALCULATION

In this multicentre study enrolling 600 patients from sites with different health settings in Asia Pacific region, we aim to test the hypothesis whether using a doctor-nurse-HCA team will reduce all diabetes-related clinical endpoints and improve control of risk factors compared to usual care, in low, middle and high-income areas including public and private clinics as well as hospital or community-based clinics.

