We also estimate the sample size needed to confirm the benefits of team-based care on controlling multiple risk factors. Apart from LDL-C goal, which can readily be achieved by initiating patients on statin therapy and thus requires a larger number to detect the small difference between the usual care and structured care groups, we estimate that 300-600 patients will be needed to confirm the superior effects of structured care. Given the expected heterogeneity in clinic settings, patient profiles and health care systems amongst different sites, a sample size of 600 patients will give each site sufficient power to confirm the superior effects of team-based structured care within their own clinic setting.

|                                         |      |      |      |
|-----------------------------------------|------|------|------|
| % of patients at 2 ABC goals in JADE-AP | 0.36 | 0.3  | 0.12 |
| SC (increased by 2-fold)                | 0.72 | 0.6  | 0.24 |
| UC (increased by 50%)                   | 0.54 | 0.45 | 0.18 |
| absolute difference                     | 0.18 | 0.15 | 0.06 |
| 80% at 0.05 alpha each group            | 123  | 186  | 756  |
| total sample size                       | 246  | 372  | 1512 |
| assuming 20% attrition rate             | 295  | 446  | 1814 |
| number needed to treat                  | 6    | 7    | 17   |

| Risk factors
units                          | A1c
% | A1c
% | SBP
mmHg | SBP
mmHg | LDL-C
mmol/l | LDL-C
mmol/l | BW   | BW    |
|------------------------------------------------|----------|----------|-------------|-------------|-----------------|-----------------|------|-------|
| reduction in risk factors compared to baseline | 0.5      | 1        | 5           | 10          | 0.5             | 1               | 0.03 | 0.05  |
| proportion of patients in SC                   | 0.77     | 0.61     | 0.46        | 0.35        | 0.32            | 0.16            | 0.16 | 0.087 |
| proportion of patients in UC                   | 0.6      | 0.44     | 0.29        | 0.18        | 0.26            | 0.09            | 0.06 | 0.026 |
| absolute difference                            | 0.17     | 0.17     | 0.17        | 0.17        | 0.06            | 0.07            | 0.1  | 0.061 |
| 80% at 0.05 alpha each group                   | 128      | 146      | 138         | 117         | 930             | 378             | 172  | 256   |

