## **DATA ANALYSIS**

All data will be analyzed using the SPSS statistical software (Windows 13.0 version, Chicago, USA). A p value of 0.05 or less (2-tailed) will be considered significant. For the primary composite endpoint, an intention to treat analysis will be performed including all patients randomized to both groups who have at least returned for one visit or contacted by phone once post randomization to ascertain clinical status (alive, dead or hospitalized). Descriptive analysis will be used to report all clinical and laboratory parameters. Student's t-test, Chi-squared test and Analysis of Co-variance will be used for between-group and within-group comparisons for all baseline data and endpoints, as appropriate. Kaplan-Meier curve analysis will be used to compare the incidence of primary composite endpoint between the JADE and DIAMOND group adjusted for age, sex, ethnicity and disease duration. Interaction between group assignment and covariates including age, gender, duration of diabetes (< or ≥8 years), socioeconomic group, complications, risk factors, JADE risk categories, compliance and psychological health parameters will be examined. Logistic regression will be used to determine independent predictors for achieving primary composite endpoint using all relevant covariates including age, gender, duration of diabetes (< or ≥8 years), centre characteristics, socioeconomic group, risk levels, metabolic and risk factor control, compliance, self care, psychological health parameters and intervention groups.

A per protocol analysis will be performed in the JADE group with details of intervention, where we shall compare baseline clinical profile, care processes, number of visits and use of medications between patients who develop and those who do not develop clinical endpoints. A sensitivity analysis will also be performed using hazard rates of the JADE and DIAMOND group amongst those who have defaulted.

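### Centre characteristics are tested as predictors in an ordinary patient-level logistic regression, so their p-values would be too small if event risk differs between centres

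*Protocol*

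**What the plan says.** The Data Analysis section names one model for this question: "Logistic regression will be used to determine independent predictors for achieving primary composite endpoint using all relevant covariates". The list of covariates begins with patient-level items and ends with "centre characteristics, socioeconomic group, risk levels, metabolic and risk factor control, compliance, self care, psychological health parameters and intervention groups". The criterion, stated once for all analyses, is "A p value of 0.05 or less (2-tailed) will be considered significant".

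Nowhere does the protocol mention a centre term, a random effect or a variance that respects clustering. The adjustment set for the Kaplan-Meier comparison is age, sex, ethnicity and disease duration; centre is not in it.

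Other sections set the context:

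- The Sample Size Calculation section describes sites "in low, middle and high-income areas including public and private clinics as well as hospital or community-based clinics". These are properties of a clinic, shared by all its patients.
- The Secondary composite outcome section plans 600 patients per site "Given the expected heterogeneity in clinic settings, patient profiles and health care systems amongst different sites".
- The section on default and missing data asks each site to define its own usual care.
- Setting and Patients recruits 600 patients per centre, "with randomization to either the JADE or DIAMOND group in a 1:1 ratio".

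**The concern.** An ordinary logistic regression treats every patient as an independent observation of every covariate. For age or disease duration that is roughly right. For public versus private, hospital versus community, or income area, about 600 patients repeat one value. Their outcomes also share whatever else is particular to that clinic, such as referral pattern, local practice or completeness of event capture. The model's standard error is correct only if centres do not differ in event risk beyond the modelled covariates. The protocol expects the opposite.

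At stake is a reported finding that a type of clinic independently predicts more or fewer diabetes-related events, when it reflects chance differences among a small number of clinics. The protocol offers its results as a guide to redesigning health care models, so such a statement could be taken up.

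**Working it through.** **Inputs from the protocol**

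- Two-sided alpha 0.05 (Data Analysis).
- 600 patients per site (Abstract; Setting and Patients).
- Attrition 20% (Sample Size Calculation), so 600 × 0.8 = 480 analysed per centre at the low end.
- Two-year event proportions at a hazard ratio of 0.8: 0.10 v 0.08 (high risk) and 0.06 v 0.048 (moderate risk). The means over the two arms are 9% and 5.4%.

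**Input not in the protocol (assumed)**

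- The residual intraclass correlation (ICC) of the primary event within centre, after patient covariates. Range taken: 0.0005 to 0.02.

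**Step 1. The plan's own sample sizes, and the number of centres they imply.** The two-proportion formula with continuity correction, 80% power and two-sided 0.05 gives:

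- 0.10 v 0.08: 3313 per arm, 6626 in total. This matches the table.
- 0.06 v 0.048: 5734 per arm, 11468 in total; × 1.2 = 13762. This matches the table.

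The quoted range of 6626 to 13762 therefore joins a total before attrition to one after it. On a single basis, rounding sites up:

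- Before attrition: 6626/600 = 11.04 and 11468/600 = 19.1, so 12 to 20 centres.
- With attrition: 7951/600 = 13.3 and 13762/600 = 22.9, so 14 to 23 centres.

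The protocol states no number of centres; these are inferences.

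**Step 2. Inflation for a covariate that is constant within a centre.** With m patients per centre:

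- Design effect DE = 1 + (m − 1) × ICC.
- Actual false-positive rate of the unadjusted Wald test = 2 × [1 − Φ(1.96/√DE)].

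Example with m = 600 and ICC = 0.002: DE = 1 + 599 × 0.002 = 2.198, √DE = 1.48, 1.96/1.48 = 1.32, and the rate is 18.6%.

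| Assumed ICC | DE, m = 480 | DE, m = 600 | False-positive rate, m = 480 | False-positive rate, m = 600 |
|---|---|---|---|---|
| 0.0005 | 1.24 | 1.30 | 7.8% | 8.6% |
| 0.001 | 1.48 | 1.60 | 10.7% | 12.1% |
| 0.002 | 1.96 | 2.20 | 16.1% | 18.6% |
| 0.005 | 3.40 | 4.00 | 28.8% | 32.7% |
| 0.01 | 5.79 | 6.99 | 41.5% | 45.9% |
| 0.02 | 10.58 | 12.98 | 54.7% | 58.6% |

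Over this range the model's standard error is too small by a factor of √1.24 = 1.1 to √12.98 = 3.6.

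**Step 3. What these correlations mean.** At an event proportion of 9%, the between-centre standard deviation is √(ICC × 0.09 × 0.91). This is 0.6 percentage points at ICC 0.0005, 1.3 at 0.002 and 4.0 at 0.02.

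**Step 4. Simulation.** Beta-binomial centre effects were simulated with 11, 12 and 23 centres, m of 480 and 600, event proportions of 5.4% and 9%, and 10,000 runs per setting. About half the centres carried the characteristic, and there were no patient covariates. For ICC from 0.001 to 0.02 the rates agreed with the formula to within about 1.5 points. The rate depended on m and the ICC and hardly on the number of centres. A t-test on centre-level proportions in the same data held 4.5% to 5.4%.

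**Step 5. The randomized comparison.** Allocation is 1:1 among individual patients, from a list prepared for each site. A shift in event risk shared by a centre's patients falls equally on both arms and cancels in their difference. The design effect above therefore does not apply to it.

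**The case against.** The strongest objection is that the point rests on silence. The covariate list is open-ended, a centre term is not excluded, and the variance specification of a secondary model is often left to an SAP, which was not available here. This stands in part: one cannot say that the analysts will ignore centre. But the protocol does name a model, a cluster-level covariate and a significance threshold, and applying those as written gives invalid p-values for that covariate. That is a stated method needing correction, not just an absent detail.

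Second, the size is assumed. The model also holds risk level, metabolic control, compliance and socioeconomic group, which would absorb part of the between-centre variation. The simulation had no such covariates. This stands, so the ICC must be read as residual, and the lower rows of the range matter as much as the upper ones. The country table of ABC target attainment gives an ICC of 0.093 for reaching at least two targets. A reader might take that as support for the upper end, but it concerns another endpoint, countries rather than centres, and unadjusted proportions.

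Third, the question is prognostic. The Sample Size Calculation section aims at the effect of team care across settings. The main effect of a centre characteristic on event risk does not answer that, nor any listed hypothesis or objective. This stands and limits the importance of the point.

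**Conclusion.** The point holds for p-values and intervals of centre characteristics in the predictor model. If the residual ICC is 0.0005 to 0.02, with 480 to 600 patients per centre, a nominal 5% test has a false-positive rate of about 8% to 59%: 8–9% at 0.0005, 11–12% at 0.001, 16–19% at 0.002, 42–46% at 0.01 and 55–59% at 0.02. No single figure in this range can be called the true rate, because the protocol gives no ICC.

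A reader might infer that the trial's main result carries such an error rate. The documents do not support that: randomization is by patient within centre, so this inflation does not reach the treatment comparison. Nor does it show that the aim of testing team care across settings fails, since this model does not test that aim. The point is worth correcting but confined to a secondary analysis.

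**What to change.** In the Data Analysis section, state that the predictor model includes a random centre intercept, with the patient-level covariates kept in it. Alternatively, use two stages: estimate each centre's patient-adjusted event rate, then regress these values on the centre characteristics.

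In either case, judge centre characteristics on between-centre degrees of freedom: the number of centres minus the number of centre-level parameters, including the intercept. One binary characteristic leaves centres minus 2. Income area in three levels (2 parameters), public or private (1) and hospital or community (1), with the intercept (1), use 5. That would leave 7 degrees of freedom with 12 centres and 18 with 23.

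The change is one sentence and a different model call, with no new data or patients. The price is wider intervals for centre characteristics and few degrees of freedom, so only a few can be examined together and they should be chosen in advance.

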### Intervention – JADE Group

In the JADE group, the patients are managed by a team of doctor, nurse and HCA, who share different tasks ranging from clinical diagnosis, education, data management and treatment to targets in order to improve the logistics in delivering this complex care protocol, augmented by information technology.

[figure not shown]

- 1) Patients randomized to the JADE group will be followed according to the protocol based on their risk levels. In addition to the CA visit, all subsequent FU visits will be documented followed by data entry into the JADE portal with issue of reports to both patients and doctor to promote sharing of information and informed decisions.

| Risk stratification                           | Very-high risk
4                                                 | High risk
3 | Medium risk
2 | Low risk
1 |
|-----------------------------------------------|---------------------------------------------------------------------|----------------|------------------|---------------|
| Cardiovascular renal complication             | ≥ 1                                                                 | 0              | 0                | 0             |
| Any risk score                                | NA                                                                  | ≥ SP           | ≥ ST and < SP    | < ST          |
| Stratification parameters                     | NA                                                                  | ≥ 3            | 2                | 0-1           |
| eGFR                                          | NA                                                                  | < 60           | 60-90            | ≥ 90          |
| Recommended number of medical visits per year | 6 or more                                                           | 4 or more      | 3 or more        | At least 2    |
| Comprehensive assessment                      | Every 12-18 months                                                  |                |                  |               |
| Other recommendations                         | Counselling/laboratory tests/telephone calls between medical visits |                |                  |               |

Parameters for risk stratification:

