|          |                     | 19%            | cataract        |
|          |                     | 37%            | microvascular   |
|          |                     | 43%            | PVD             |

| Steno 13 year FU       | SC=80 | UC=80 | HR   |
|------------------------|-------|-------|------|
| death                  | 24    | 40    | 0.50 |
| CVD-death              | 9     | 18    | 0.23 |
| MI                     | 8     | 21    | 0.26 |
| stroke                 | 6     | 18    | 0.23 |
| PCI                    | 8     | 13    | 0.16 |
| revascularization      | 6     | 10    | 0.13 |
| amputation             | 6     | 14    | 0.18 |
| all CVD events         | 25    | 48    | 0.60 |
| cancer-death           | 2     | 5     | 0.06 |
| DM nephropathy         | 20    | 37    | 0.46 |
| ESRD                   | 1     | 6     | 0.08 |
| Blindness              | 2     | 7     | 0.09 |
| Progression of DMR     | 41    | 54    | 0.68 |
| Laser or macular edema | 14    | 27    | 0.34 |

| 2-year SURE Study | ≥3 target | <3 targets | HR   |
|-------------------|-----------|------------|------|
| ESRD/death/dSeCr  | 14        | 34         | 0.30 |
| dialysis          | 6         | 12         | 0.11 |
| dSeCr             | 10        | 21         | 0.18 |
| death             | 4         | 15         | 0.13 |
| MI/angina/PCI     | 4         | 7          | 0.06 |
| heart failure     | 12        | 16         | 0.14 |

| 7-year AJMC paper | SC | UC | HR   |
|-------------------|----|----|------|
| death             | 8  | 20 | 0.25 |
| death/CVS/renal   | 20 | 30 | 0.38 |

These Kaplan-Miere plots show the estimated events from these 3 studies in a 2-year period.

Chinese T2D patients with CKD (eGFR 30 ml/min/1.73m^2)  
Chan JC et al Diabetes Care 2009

[figure not shown]

Chinese T2D patients with HT (no CVD/CKD)  
So WY et al Am J Managed Care 2003

[figure not shown][figure not shown]

Caucasian T2D patients with microalbuminuria (no CVD/CKD)  
Gaede P et al NEJM 2008

[figure not shown]

Using validated risk equations and risk parameters, the JADE Program stratified patients into very high risk, high risk, medium risk and low risk groups with respective estimated annual event rate of 7%, 3%, 1.5% and 1%.

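### The analysis labelled per protocol compares visit counts by outcome within JADE only: the label is wrong, and the bias can go either way or cancel, depending on how visits are counted

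*Protocol*

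**What the plan says.** After the intention-to-treat analysis of the primary composite, the protocol's Data Analysis section states: "A per protocol analysis will be performed in the JADE group with details of intervention". The grouping is by whether a patient has an endpoint: "we shall compare baseline clinical profile, care processes, number of visits and use of medications between patients who develop and those who do not". The population (JADE only), the grouping variable (the outcome) and one compared quantity (a visit count) are thus fixed. The section lists t-tests, chi-squared tests and analysis of covariance for comparisons, and adds: "A p value of 0.05 or less (2-tailed) will be considered significant". For this analysis it states no counting window, no scaling to follow-up time and no adjustment for risk level.

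Two other sections bear on it:

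- Intervention – JADE Group: "Patients randomized to the JADE group will be followed according to the protocol based on their risk levels". The table row headed "Recommended number of medical visits per year" gives 6 or more (very high risk), 4 or more (high), 3 or more (medium) and at least 2 (low).
- Sample Size Calculation, Primary composite outcome: patients are stratified into "very high risk, high risk, medium risk and low risk groups with respective estimated annual event rate of 7%, 3%, 1.5% and 1"%.

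The composite in Outcome Measures contains death, but also many non-fatal components after which a patient can keep attending.

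**The concern.** A per-protocol analysis normally compares the randomised arms among patients who followed the assigned strategy. This one has no adherence criterion and no comparator. Because it is described alongside the intention-to-treat analysis, a reader may take it for the per-protocol counterpart of the primary result.

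The visit comparison has a second problem. A visit count builds up over follow-up, and here it is compared according to an outcome that occurs during that same follow-up. Two mechanisms produce a difference without any effect of visits:

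- **Truncation.** A patient who dies, or whose count stops at the event, has less time in which to make visits. This lowers the count in event patients.
- **Schedule.** The same risk level sets both the planned number of visits and the event rate. This raises the count in event patients.

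Visits are a core part of what JADE delivers, so a difference in either direction, or no difference, invites a conclusion about whether the delivered care prevents events.

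**Working it through.** **Inputs from the protocol.** Visits per year v = 6, 4, 3, 2 and annual event rates λ = 0.07, 0.03, 0.015, 0.01 for very high, high, medium and low risk; follow-up 2 years (the stated minimum); 300 JADE patients per site; two-sided 0.05. The only stated figure on visit volume (Manpower estimation) reproduces: 300 × 4 = 1200 patient-visits a year.

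**Assumptions.** The text says most enrolled patients were high or very high risk but gives no shares. Four mixes (very high/high/medium/low, %) are used: 20/55/20/5, 40/45/12/3, 10/60/25/5 and 25/25/25/25. Visits occur at the scheduled number, event times are exponential, and visits have no effect on events. A share s of events stops the visit count.

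**Step 1: schedule only (s = 0), mix 20/55/20/5.** The two-year event probability is p = 1 − exp(−2λ) = 0.1306, 0.0582, 0.0296, 0.0198.

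- Overall event probability: 0.20×0.1306 + 0.55×0.0582 + 0.20×0.0296 + 0.05×0.0198 = 0.0651.
- Two-year visits are 12, 8, 6, 4. Their probability-weighted sum in event patients is 0.609, so their mean is 0.609/0.0651 = 9.36.
- The overall mean is 0.20×12 + 0.55×8 + 0.20×6 + 0.05×4 = 8.20, so the mean without events is (8.20 − 0.609)/(1 − 0.0651) = 8.12.
- Difference: +1.24 visits.

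**Step 2: all counts stop at the event (s = 1).** Given an event within two years, its mean time is 1/λ − 2·exp(−2λ)/p = 0.977, 0.990, 0.995, 0.997 years, about half of follow-up. The event-patient mean falls to 4.61, and the difference is 4.61 − 8.12 = −3.51.

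**Step 3: part of the events stop the count.** The difference is linear in s: 1.24 − s × (9.36 − 4.61). It is zero at s = 1.24/4.75 = 0.26.

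**Step 4: all mixes.**

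| Mix | s = 0 | s = 0.25 | s = 0.5 | s = 1 | Zero at s |
|---|---|---|---|---|---|
| 20/55/20/5 | +1.24 | +0.06 | −1.13 | −3.51 | 0.26 |
| 40/45/12/3 | +1.28 | −0.05 | −1.37 | −4.03 | 0.24 |
| 10/60/25/5 | +0.95 | −0.14 | −1.23 | −3.41 | 0.22 |
| 25/25/25/25 | +2.25 | +1.02 | −0.20 | −2.65 | 0.46 |

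**Step 5: how often a t-test is significant.** Simulation with Poisson visits, 600 runs per scenario and no visit effect, over the four mixes, gave these proportions of p < 0.05:

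| Scenario | 300 JADE patients | 3000 (assumed) |
|---|---|---|
| Truncation only, same schedule and rate for all | 0.995–1.00 | 1.00 |
| Schedule only | 0.24–0.63 | 0.96–1.00 |
| Both, s = 1 | 0.77–0.995 | 1.00 |
| Both, s = 0.5 | 0.10–0.42 | 0.15–1.00 |
| Both, s = 0.25, three mostly high-risk mixes | 0.07–0.10 | 0.09–0.14 |
| Both, s = 0.25, equal mix | 0.22 | 0.88 |
| Neither mechanism | 0.04–0.08 | 0.05–0.06 |

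With both mechanisms removed the error rate is near nominal, so the excess comes from the mechanisms.

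**The case against.** The strongest reply is that this is a profile description. Visits are one of four items compared, the protocol draws no causal conclusion from them, and the effect claim rests on the randomised comparison. That stands as far as the primary analysis goes. It does not rescue the label, since the protocol calls the analysis per protocol, not descriptive.

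A second reply is that the counting window belongs in a statistical analysis plan, which may exist. The exact window can indeed be left there. But counting raw visits to the event and counting them to study end are both biased, so choosing between those windows does not repair the comparison.

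Third, the schedule gradient may be narrower than the table suggests. The table gives minimums, while Study Design and the JADE intervention steps have reviews every 2–4 months, which is 3 to 6 a year. Which applies to low-risk patients is for the sponsor to reconcile. The effect here is small: with 3 instead of 2 visits a year at low risk, the schedule-only difference in the 20/55/20/5 mix is +1.17 instead of +1.24.

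A reader might infer that the analysis is bound to show a strong association, since truncation alone gives about 4 against 8 visits and significance in at least 99.5% of runs. The documents do not support this. That figure needs every count to stop at the event, which the protocol does not state, and the same schedule for all patients, which contradicts its own table. Only death necessarily ends attendance, and the two mechanisms oppose each other.

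**Conclusion.** The concern holds in this form. The label is wrong: there is no adherent population and no comparison with DIAMOND. The raw visit comparison is biased, with a sign and size that depend on how visits are counted. With no true visit effect, the expected difference runs from about +1 to about −4 visits in the three mostly high-risk mixes, and from about +2.2 to −2.6 in the equal mix. It passes through zero when roughly a quarter of events (nearly half in the equal mix) stop the count. A significant result may be an artefact and a null result may be cancellation, so neither is interpretable.

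The direction of each mechanism follows from the protocol's own visit table and event rates. The sizes rest on the assumed risk mixes, stopping shares, attendance at the scheduled number and two-year follow-up. The primary intention-to-treat comparison is not affected. This is a worthwhile improvement to a supporting analysis, not a threat to the trial's main conclusion.

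**What to change.** In Data Analysis:

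1. Rename the analysis a descriptive within-JADE analysis and remove the term per protocol.
2. Replace the raw visit comparison with attendance expressed as a share of the visits scheduled for the patient's risk level.
3. Analyse it either by landmark (attendance in months 0–12 against first events after month 12) or in a Cox model with attendance as a time-varying covariate.
4. Adjust for baseline JADE risk level, and label the result exploratory and non-causal.

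A comparison of adherent JADE patients with all DIAMOND patients should not be added in its place. It would break the randomisation and bring in selection of patients who adhere, which adjustment for baseline risk alone does not remove.

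The cost is wording only. The landmark version drops first-year events: at a constant hazard over two years their share is 1/(1 + exp(−λ)), which is 0.51 at λ = 0.034 (the mean rate in the 20/55/20/5 mix), so roughly half. The Cox version keeps them. In both versions attendance remains self-selected, so a residual association still cannot be read as an effect of visits.
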